Independent Evaluators (IE) who are blinded to the study procedures and treatment assignments will collect data at 6 and 12 months by phone. They will mail assessment packets to participants and then work with them to complete all self-report items. IEs will arrange a lab visit for a blood draw within 2 weeks before and 2 weeks after the target data-collection time (facilitated by PCPs). If PCPs have already obtained A1c levels in that timeframe, those values will be used. Participants will receive modest compensation after A1c results and self-report assessments are collected. RAs will also perform chart abstraction of clinical baseline, moderating, and exploratory variables. Data Quality Assurance: Using previously developed and standardized procedure manuals, providing rigorous training and fidelity measurement of study coaches and independent evaluators, as well as providing written guides for assessments are ways quality will be assured. Attrition/Retention and Missing Data: We expect rates of missing data for primary outcomes less than 25%, leading to primary outcome data for greater than 75% of participants. To evaluate the potential relationship between loss to f/u and outcome variables, reasons for study discontinuation will be recorded for subsequent analyses, and overall attrition rates will be factored in the analyses of the primary specific aim. We will conduct sensitivity analyses using tests for data missing completely at random and tests for nonrandom missingness. We will also plot the data over time to visually assess changes in outcomes from baseline to 12 mos. and to indicate whether additional terms are needed in the models to account for nonlinearity over time. Data Analysis Plan: Primary Analyses: A1c and Depression Outcomes--We will compare participants in the two study arms on baseline characteristics, including sociodemographic characteristics (age, race/ethnicity, gender, education level, independent living status, VA copay status, employment status) and clinical variables (BMI, Deyo comorbidity score, psychotropic and diabetes medications and treatments, specific psychiatric diagnoses, and number of PCP visits in the previous 12 mos). Based on recommendations of the CONSORT group, we will not provide tests of significance or adjust subsequent analyses for variables found to differ because adjustment may bias the estimated treatment effect. However, the analyses for the primary aim will be adjusted for variables we have decided a priori may be important to control: a) baseline values of HbA1c and PHQ-9, b) whether the patient was on exogenous insulin, and c) the stratification variable, site. In addition, we will compare participants on d) access to psychotherapy and medication, defined as dichotomous variables. At baseline, 6 months, and 12 months, we will construct variables for whether the patient was receiving

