
psychotherapy during the previous 6 months (yes/no), whether psychotropic medications were started or changed during the past 6 months (yes/no), and whether insulin was added during the past 6 months (yes/no). A1c and Depression Outcomes at 6 months--The patients' A1c levels and PHQ-9 scores at 6 months will be the primary outcomes. We will examine the normality of the distributions of these outcomes and will consider transformations such as the log or the inverse, if necessary. Separate models will be run for HbA1c and for PHQ-9. We will run hierarchical linear model analyses to account for the correlation of patients being seen by the same PCP. Using this nested approach, we will test if there are differences between EUC and the HOPE intervention, using the A1c level and the PHQ-9 score (either untransformed or transformed, if needed) as dependent measures. Although patients are also nested within coach, the coaches are not assigned exclusively to certain PCPs. We will include intervention fidelity scores for each coach as a study variable in our analysis of this aim to account for coaching fidelity effects. Each model will contain a variable indicating the treatment group, indicator variables representing site, whether or not the patient was on exogenous insulin (evidence suggests that insulin use impacts both A1c and depressive symptoms), receiving psychotherapy, taking psychotropic meds, and baseline A1c or PHQ-9 levels as independent variables. A significant value for the treatment group variable in the hierarchical model will indicate that there were statistically significant differences between the intervention and EUC. In addition, we will examine whether the groups differed as to whether or not they had clinically significant changes in A1c and PHQ-9 by dichotomizing the outcomes. A significant decrease for A1c is defined as 0.5 between each time point and from baseline to 12-months. For PHQ-9, this will be a change score of 5 or greater at 6- and 12-months. We will test whether the two groups (clinically significant change vs. no change) differed using a hierarchical logistic-regression model in which the dichotomous outcomes are the dependent variable. The independent variables will be those described above for the hierarchical linear regression. A1c and Depression Outcomes at 12-months-- The patients' A1c levels and PHQ-9 scores at 12-months will be the primary outcomes. Similar to the analyses at 6 months, we will examine the distribution and run hierarchical linear models on the 12 month data. In addition, we will examine all of the time periods in a hierarchical longitudinal analysis, separately for A1c and PHQ-9. This random coefficient model will allow us to fit a line for each participant using his/her available data, including participants with missing values, and will maximize the power to detect differences because patients are not removed from the analysis if any of the time periods is missing. Patients will be nested with their PCP. The model will contain the A1c and PHQ-9 values for each of the time periods (baseline, 6 and 12 months). The independent variables in the model will be time, treatment, the interaction of time and treatment, site, and use of exogenous insulin psychotropic meds, or psychotherapy. The treatment effect will measure differences between the intervention and EUC groups at baseline, and the time effect will measure whether there was an overall change over time in the two clinical outcomes. The time-by-treatment interaction is of most interest in the longitudinal analysis because a significant value will indicate that there was a difference between the intervention and EUC groups over the 12-month time period. Mediators and Moderators: To examine the role of potential moderators and mediators on intervention effectiveness, we will evaluate factors that mediate and moderate outcomes at 6 and 12 months. Moderating variables are those that specify on whom and under which conditions treatments have different effects. The moderating variables for this aim include sociodemographic traits, BMI, medical and psychiatric comorbidity, and social support. Mediator variables identify possible mechanisms through which a treatment achieves its effect. Mediators include the GET-D scores for goals and action plans, diabetes-related distress, self-efficacy, performance of self-care behaviors, and adherence to pharmacological therapy. We will consider the difference between the moderators and mediators in terms of when they occur relative to treatment and whether they are correlated with treatment. Moderators must precede treatment and should not be correlated with treatment. Mediators will occur during treatment and should be correlated with treatment. Thus, we will initially test for the association of the moderating and mediating variables with treatment. Since the treatment is a dichotomous variable, we will use t tests to determine if continuous moderators or mediators are associated with treatment and chi-square tests to determine if ordinal or categorical moderators or mediators are related to treatment. After verifying that a possible moderator is not significantly related to treatment, we will run the model, including a term in the model for the moderator and a term for the interaction of that variable with treatment. A significant value for the interaction term will indicate that the effect of treatment on the individual patients depends on their value of the moderator. For mediators, we will test if the variable has either a main or interactive effect on the outcome. With an emphasis on the effect size of treatments and what influences the effect size for a particular moderator or mediator, we will calculate effect sizes at each of the scheduled time points. In addition, we will form response categories to assess the stability of variables under two approaches to measuring outcomes (one using continuous variables for outcomes and the second using categories for the outcomes). For example, we might define an improvement in A1c as a decrease of 0.5 from baseline or PHQ-9 decrease of 5 from baseline. We would then run the analytic models using the dichotomous variable of whether or not the patients' A1c level improved as the outcome variable. If the two-variable presentations prove to be similar, we will likely use the categorical approach because of greater ease in reporting results to

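### Exploratory Aim 2 fits a treatment-by-moderator model only if the baseline variable passes a significance test against the randomised arm; the pre-test adds no validity and screens out sound moderators by chance

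*Protocol*

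**What the plan says.** Section G2 of the Protocol, in its part on mediators and moderators, defines the two kinds of variable by their timing and their relation to treatment. On moderators it says: "Moderators must precede treatment and should not be correlated with treatment". The list reads: "The moderating variables for this aim include sociodemographic traits, BMI, medical and psychiatric comorbidity, and social support".

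The definition is then turned into a test: "Thus, we will initially test for the association of the moderating and mediating variables with treatment". The tools are named: "we will use t tests to determine if continuous moderators or mediators are associated with treatment and chi-square tests" for ordinal or categorical variables. The moderator and its interaction with treatment enter a model only afterwards: "After verifying that a possible moderator is not significantly related to treatment, we will run the model". No sentence says what happens to a moderator that does show an association, and no significance level is given for this step.

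Earlier in G2, under the primary analyses, the plan lists the baseline characteristics to be compared between arms, and cites CONSORT in saying: "we will not provide tests of significance or adjust subsequent analyses for variables found to differ because adjustment may bias the estimated treatment effect".

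Section D labels the moderator and mediator work as exploratory Aim 2. Section F1 randomises individual patients, stratified by site, with 146 to HOPE and 96 to EUC. Section F2 places randomisation after the baseline assessment and blood draw.

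**The concern.** A moderator measured before randomisation is independent of arm by design. A significance test of that independence asks a question whose answer is already known, so among all randomised patients every significant result is a false alarm. Letting that result decide whether an interaction is examined makes the set of reported moderators depend partly on chance imbalance. A variable named in advance, including one that truly modifies the effect, may go unreported for a reason unrelated to its merit.

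The step also departs from the reasoning the plan accepts elsewhere. It declines to test baseline variables by arm in one place, then tests largely the same variables by arm in another and lets the p-value steer the analysis.

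At stake is the completeness of an exploratory analysis. Hypotheses 1a and 1b and the sample size do not depend on it.

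**Working it through.** The protocol states no figure for this step, so there is none to reproduce. The check has four parts.

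**1. Is independence already guaranteed?** Moderators precede treatment (G2). Randomisation follows baseline (F2) and is at patient level (F1). For the full randomised set, independence of moderator and arm is therefore met by design. A pre-test at level α rejects with probability of about α for each patient-level moderator.

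**2. How often would at least one moderator be lost?**

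Inputs:
- α: not stated for this step. I assume 0.05, the two-sided level in the sample-size section (G1), and vary it from 0.01 to 0.10.
- Number of moderators k: not stated. G2 names sociodemographic traits, BMI, medical comorbidity, psychiatric comorbidity and social support. Counted as written, that is 5. If the traits are the seven in the baseline list ("sociodemographic characteristics (age, race/ethnicity, gender, education level, independent living status, VA copay status, employment status"), it is 7 + 4 = 11.
- Independence between the tests: assumed.

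Formula: P(at least one lost) = 1 − (1 − α)^k.

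| k | α | Calculation | Result |
|---|---|---|---|
| 5 | 0.05 | 1 − 0.95^5 | 23% |
| 11 | 0.05 | 1 − 0.95^11 | 43% |
| 11 | 0.01 | 1 − 0.99^11 | 10% |
| 11 | 0.10 | 1 − 0.90^11 | 69% |

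**3. How large an imbalance trips the test?** With 146 and 96 patients and a critical value of about 1.97, the threshold is 1.97 × √(1/146 + 1/96) = 0.26 standard deviations.

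**4. Does the pre-test protect the interaction estimate?** I simulated 20,000 trials with 146 and 96 patients, a standard normal moderator, unit residual variance and a true interaction of 0.40. The t test at 0.05 dropped the moderator in 5.1% of trials. The mean interaction estimate was 0.400 in trials that passed and 0.401 in trials that were dropped, with standard deviations of 0.133 and 0.135. The pre-test does not separate good estimates from bad ones. Equally, it does not bias those it lets through. The harm is lost analyses and selective reporting.

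**Comparison with the baseline rule.** The baseline list in G2 includes the sociodemographic items, BMI, the Deyo comorbidity score and psychiatric diagnoses. The moderator list covers sociodemographic traits, BMI, and medical and psychiatric comorbidity. Of the named moderators, only social support is absent from the baseline list.

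**The case against.** Several points on the other side are fair.

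- **Scope.** The analysis is exploratory and no confirmatory conclusion rests on it. This stands and limits the severity. The Aim 2b factors are studied within the HOPE arm, so a test against arm does not apply to them.
- **The baseline rule has another purpose.** A reader might infer that the plan flatly contradicts itself. The documents do not support that. The refusal to test stands under the primary analyses and concerns the baseline comparison and adjustment of the treatment effect. The pre-test is meant to tell moderators from mediators. What remains is an inconsistency of principle over largely the same variables.
- **The pre-test might detect something real.** A reader might infer that it can never do so. That holds only for all randomised patients. The protocol allows for 25% attrition at one year and does not say which set is tested. Among patients with outcome data, differential attrition could produce a genuine association. The plan does not give this as the purpose, and skipping a moderator would not correct attrition bias.
- **The percentages are assumed.** The significance level, the count and independence are all assumptions. Sociodemographic items are plausibly correlated. Section D also names diabetes distress, self-efficacy and facility-level availability of mental health services as possible mediators or moderators, so 11 is not a firm count. A facility-level variable would rarely fail, because randomisation is blocked and stratified by site. A reader might also take 43% as the chance of losing a true effect modifier. It is the chance that any one of 11 listed variables fails. For a given patient-level moderator the chance is about 5% at a level of 0.05.
- **Discarding is inferred.** The plan says when the model will be run, not what follows a failed test. Not running the model is the natural reading, but a statistical analysis plan that is not shown could say otherwise.

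**Conclusion.** The point holds for exploratory Aim 2. As written, the pre-test makes the interaction model depend on a chance result and gives no validity in return. Its cost is a loss probability per valid patient-level moderator equal to the level used, about 5% if that level is 0.05. The chance of losing at least one is 23% to 43% for 5 to 11 independent moderators at 0.05, and 10% to 69% for 11 across levels of 0.01 to 0.10. These joint figures are illustrations. The mechanism needs only patient-level randomisation, measurement before treatment, and testing in all randomised patients.

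The conflict with the baseline rule is one of principle and does not amount to two opposing rules for one analysis. Severity is low to moderate, because the primary comparison is unaffected.

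**What to change.** In the mediator and moderator part of G2:

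1. Delete the association-with-treatment pre-test for baseline moderators. State instead that independence from arm follows from randomisation and measurement before treatment.
2. List the baseline moderators by name. Assign variables that could take either role, such as diabetes distress and self-efficacy, by time of measurement: the baseline value as moderator, the value during treatment as mediator.
3. Fit the treatment interaction for every listed baseline moderator and report all estimates with confidence intervals, labelled exploratory.
4. Keep the association-with-treatment step for mediators, which arise after randomisation and may properly be related to arm.

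The cost is a short text change plus the work of settling the variable list and roles in advance. No further patients, visits or data are needed.

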2.) To examine the role of potential moderators and mediators on intervention effectiveness. Exploratory Aim 2a. To evaluate factors that mediate or moderate effectiveness at 6 and 12 months for all enrolled patients. Potential mediating and moderating variables include patient-level (diabetes distress and self-efficacy and sociodemographics) and facility-level (availability of mental health services) factors. Exploratory Aim 2b. To evaluate factors that mediate or moderate effectiveness at 6 and 12 months for patients in the HOPE arm. Factors include adherence (e.g., session attendance), fidelity (ratings of coach effectiveness), and treatment implementation (e.g., goal-setting quality and self-management behaviors).

3.) Evaluate the potential for embedding HOPE in VA primary care settings, using the RE-AIM framework for evaluating effectiveness of behavioral interventions. Exploratory Aim 3a - Reach. Compare clinical and demographic characteristics of participants with those of all potentially eligible patients. Exploratory Aim 3b - Adoption. Qualitatively elicit PACT clinician and participant perceptions of HOPE to prepare for implementation next steps.

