**Section F: Design/Procedure****F1. Design**

Select one category that most adequately describes your research:

z.r) Randomized, Efficacy Study -- Surgical Techniques/Interventions

Discuss the research design including but not limited to such issues as: probability of group assignment, potential for subject to be randomized to placebo group, use of control subjects, etc.

We propose a randomized clinical trial to compare the effectiveness of HOPE with that of enhanced usual primary care (EUC) for distance-based Veterans with comorbid diabetes and depressive symptoms receiving

primary care services at the VA. Randomization will occur at the patient level and be stratified by clinical site. In addition, we will evaluate the durability of the treatment over a 6-month period following the active-treatment phase. To better understand the mechanics of change, we will conduct an exploratory examination of the mediating and moderating variables associated with changes in the primary outcomes (HbA1c levels, depression symptoms) at both 6 and 12 months. Additional exploratory analyses will attempt to better understand the relative strengths, weakness, barriers, and facilitators important to future implementation if the intervention produces significant changes.

The proposed study will enroll 242 patients with diabetes and depressive symptoms who receive care in VA CBOCs throughout Southeast Texas, as well as MEDVAMC patients living >20 miles from the hospital who face similar distance related treatment barriers. 60% of the participants (n=146) will be randomized to receive 9 behavioral coaching sessions in 6 months (active intervention), followed by 6 months without coaching (maintenance period); the other 40% (n=96) will receive EUC, which will include the provision of educational materials and feedback about diabetes and depression. All consented participants (both treatment arms) and their PCPs will be notified of the diabetes control and depressive symptoms and provided with guideline-based recommendations for treatment of depressive symptoms. Randomization will be stratified by clinical site.

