
their intervention materials in the mail. Participants randomized to HOPE will be instructed to complete the consent for voice recording form and return it in a pre-provided postage paid envelope. Randomization will be blocked and stratified by site to assure balance in the number of patients assigned to HOPE or EUC at each facility. Within each site, we will use random blocks of 4 and 6. The random numbers will be generated in SAS PROC PLAN by [name]. The number of patients randomized at each site will be proportional to the number of patients estimated to be eligible for the study at that facility and adjusted as new CBOCs open and their data becomes available. Should a proportional recruitment prove difficult, we will reconsider this practice to ensure that we meet our sample size goals. Conducting EUC: All enrolled participants will receive the EUC procedures at their clinical site pertaining to diabetes care and depressive symptom management. Once participants are consented and enrolled, study personnel will: 1-Send a standardized letter to study participants notifying them of the study findings related to their diabetes A1C levels and depressive symptoms, and a reminder that their PCPs will be notified as per the informed consent (in Sect S as EUC Cover Letter). Patients will also be provided with basic educ. materials related to diabetes and depression (Sect S); 2-Enter a parallel note in the patient's CPRS record notifying the PCP of these findings, with an add'l signer request (to signify awareness of note); 3-Include recs for MH referral or treatment prompt for depression in the CPRS note; Repeat steps 1-3 after the results of the 6mo and 12mo data collection are available. No specific recs for diabetes care will be provided, no further contact will be made during the acute intervention period for participants in EUC. Conducting HOPE Intervention: Study RAs will contact participants randomized to HOPE to arrange the first behavioral call w/in a 2-3 week window. The coach will initiate calls at the participant's time and day of choosing. If a veteran fails to appear 3x for the phone appt, a letter may be sent by the staff on behalf of the coach. Like EUC, HOPE patients will receive basic educ info on diabetes and depression. A standardized behavioral counseling framework is used by coaches to guide each of the calls, regardless of the specific contents of each session. At the conclusion of each behavioral coaching call, the coach will summarize the progress of the current session and schedule the next call. The coach will then enter a note in the participant's CPRS record with the participant's PCP listed as an additional signer. This note will summarize the specifics of what was discussed during the prior coaching call and provide, in the participant's own language, the agreed upon specific goal and action plan(s). Coaches may also suggest additional f/u or referrals to the PCP, based on the participant's needs and requests, such as a referral to a diabetes educator or nutritionist. Coaches may also ask PCPs to schedule a quicker (urgent care) f/u visit if warranted. The actual request for referrals and all medical f/u appts and medication changes will be left to PCPs' discretion. HOPE Intervention modules: A total of 9 sessions will be conducted during a 6mo period. For the first 3mo, coaching sessions will be 30min, take place bi-weekly, and will include 2 core sessions and 4 elective sessions (where patient chooses topic to cover). In the next 3mo, 3 f/u sessions, each 15min long, will occur once a month. There are a total of 6 modules for the patient to choose from for their elective sessions, and modules may last more than one session. The modules assigned to elective sessions 3-6 are adaptable, and one or more may be presented in any order at the participant's and coach's discretion.

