
## Section G: Sample Size/Data Analysis

### G1. Sample Size

How many subjects (or specimens, or charts) will be used in this study?

Local: 455      Worldwide: 455

Please indicate why you chose the sample size proposed:

The proposed sample size of 455 includes 425 patients and 30 clinicians.

The sample size of clinicians was determined by creating a schedule for the expected flow of Veteran participants in the study that predicts expected demand for coaching.

In determining the sample size of patients for the study, we examined the number of patients needed to have adequate power for both hypotheses related to the primary aim (specific aim 1). The sample size determined for the primary aim was inflated to account for potential correlation of patients treated by the same PCP and to account for attrition at 1 year of 25%, based on our and other prior VA studies.

The sample size is based on testing for a clinically important difference between the two groups at a single time point, using a two-group t test with a 0.05 two-sided significance level and power of 80%. For HbA1C, a difference of 0.5 is considered clinically significant within a 6-month time frame. Using a difference score of 0.5 in the mean HbA1c between the two groups and an estimated pooled standard deviation of 1.1 results in

an effect size,  $d = .45$ . This effect size is consistent with our prior RCT study on behavioral coaching interventions which generated HbA1c level differences of 0.68 and a medium effect size of 0.50 and estimates from our HOPE pilot confirm these effects. Using these data, a sample size of 79 per group or 158 total would be needed for a significant difference in the proportion of participants achieving greater than or equal to 0.5 improvement in HbA1c.

For PHQ-9, a score of less than 10 or a 5-point decline from baseline would be considered a clinically significant improvement. The sample size of 79 per group would have 80% power to detect a change as small as 1.5 points in the PHQ-9 score with a two-sided  $\alpha = 0.05$ . From our own work using cognitive-behavioral therapy for medically ill Veterans with depression, we found clinically significant improvements in Beck Depression Scale scores consistent with effect sizes of 0.98 at 8 weeks and 1.05 at 20 weeks post-intervention. This level of efficacy is consistent with our estimates of clinically significant change as indicated by PHQ-9 scores.

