
clinicians based on response categories. Evaluating the potential for embedding the HOPE intervention within VA (Assessing Implementation): Exploration of reach--We will compare the demographic and clinical characteristics of study participants from the study sites to those of potentially eligible patients typically cared for at each CBOC and the MEDVAMC. For each site, we will test whether patients who participated differed from (a) patients who were approached but refused enrollment and (b) all remaining patients who would have met inclusion criteria but who were not included in the study, using analysis of variance for continuous variables and chi-square tests for categorical variables. The variables of interest will include age, gender, race, BMI, Deyo comorbidity score, and presence of PTSD or major depression. These variables will be obtained from the VISN 16 data warehouse. The potentially eligible patients cared for at each facility will be determined using diagnoses of diabetes and depression from the inpatient and outpatient files and A1c values from the VISN 16 data warehouse (with IRB approval). Exploration of adoption--We will evaluate the perceptions and practices of clinicians regarding intervention processes including the incorporation of behavioral goals and action plans within the progress notes and treatment plans described by PCPs. To accomplish this aim, we will purposively sample PCPs at each clinical site, including those who have cared for control and intervention subjects. We will use respondents' PACIC scores to purposively sample low and highly rated PCPs on the patient engagement and goal-setting subscales. Recruited PCPs will be evaluated using in-depth interviews to elicit their perceptions of the overall intervention procedures and their use of any constituent elements of each intervention. Consistent with established qualitative interview methodology, interviews will be audiotaped, transcribed, and analyzed using a deductive approach based on a coding system developed from our interview guide. Coded units will be reexamined for relationships and clustered into patterns. Based on past experience, we anticipate that each interview will last 30 minutes. Quantitative analyses will also be done on the coach surveys completed pre-, post-, and 6-months-post-training to assess change over time. The results of these quantitative and qualitative analyses will guide future implementation studies of the HOPE intervention in usual VA care.

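### Exploratory Aim 3a asks an overall question about reach, but the only tests specified are run site by site, with no pooled or site-adjusted comparison

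*Protocol*

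**What the plan says.** Section D lists Reach as Exploratory Aim 3a and words it as a single overall comparison: "Compare clinical and demographic characteristics of participants with those of all potentially eligible patients".

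The reach paragraph in G2 opens with the same general intention but attaches no method to it. The method follows, and its unit is the site: "For each site, we will test whether patients who participated differed from (a) patients who were approached but refused enrollment". The second comparison group, with the test for continuous measures, is described as "all remaining patients who would have met inclusion criteria but who were not included in the study, using analysis of variance for continuous variables"; categorical measures get chi-square tests. The variables are given as: "The variables of interest will include age, gender, race, BMI, Deyo comorbidity score, and presence of PTSD or major depression". That is six items as listed, or seven if PTSD and major depression are tested separately.

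For reach, the text gives no test combined over sites, no site term and no effect measure. It also gives no significance level, number of sites or comparison-group sizes. The recruitment area is described in F1 (patients who "receive care in VA CBOCs throughout Southeast Texas, as well as MEDVAMC patients living >20 miles from the hospital"), and F2 lets the site allocation be "adjusted as new CBOCs open and their data becomes available".

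**The concern.** The aim and the stated tests sit at different levels. The aim needs one answer per characteristic: are participants older, sicker or more often depressed than the patients from whom they were drawn, and by how much? The tests would return a grid of p-values by site, variable and comparison group, with no rule for combining them.

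Such a grid can mislead in two alternative situations. If there is no selection, some cells will probably be significant by chance. If there is a modest selection common to all sites, many cells may be non-significant because each holds only a fraction of the participants. G2 says the implementation analyses will guide future studies of HOPE in usual VA care, and reach is the part that bears on generalisability.

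**Working it through.** **Inputs from the protocol**
- Participants: "The proposed study will enroll 242 patients with diabetes and depressive symptoms" (F1).
- Variables: 6 or 7; comparison groups: 2 (G2).
- Sites: not stated. Plural CBOCs plus the MEDVAMC imply at least 3.
- Significance level: G1 sizes Aim 1 "using a two-group t test with a 0.05 two-sided significance level and power of 80" percent. No level is given for reach.

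**Assumptions**
- 3, 5 or 10 sites of equal size.
- Two-sided 0.05 per test.
- 1 to 20 comparators per participant.
- For the false-positive figures, independent tests and no true differences.

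**Step 1. The plan's own figure.** A two-sample t test with d = 0.45, two-sided 0.05 and 80% power gives 78.5, so 79 per group and 158 in total. Then 158 × 1.15 = 181.7, rounded to 182, and 182 × 1.33 = 242.1. The total of 242 is reproduced. This calculation covers Aim 1 only; none is given for reach.

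**Step 2. Number of tests and chance of at least one false difference.** The chance is 1 − 0.95^m, and the expected number of false differences is 0.05 × m.

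The protocol can be read in two ways. In reading A, the analysis of variance or chi-square is one three-group test per variable, so m = sites × 6. In reading B, participants are compared separately with each group, so m = sites × 6 or 7 × 2.

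| Sites | A: tests | A: chance | B: tests | B: chance | B: expected false |
|---|---|---|---|---|---|
| 3 | 18 | 60% | 36–42 | 84–88% | 1.8–2.1 |
| 5 | 30 | 79% | 60–70 | 95–97% | 3.0–3.5 |
| 10 | 60 | 95% | 120–140 | 99.8–99.9% | 6–7 |
| Pooled | 6 | 26% | 12–14 | 46–51% | 0.6–0.7 |

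Independence matters little here. A simulation of reading B with seven variables used correlation 0.5 between the two comparisons, because they share the participants, and 0 or 0.3 between variables. It gave 82–86% at 3 sites and 95–96% at 5.

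**Step 3. Power per comparison.** Two-sample t test, two-sided 0.05, n = 242 / sites participants against 1 to 20 times as many comparators.

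| Sites | Participants per site | Power, 0.3 SD | Power, 0.5 SD |
|---|---|---|---|
| 3 | 80.7 | 47–75% | 88–99% |
| 5 | 48.4 | 31–53% | 68–92% |
| 10 | 24.2 | 18–30% | 40–67% |
| Pooled | 242 | 91–99% | over 99% |

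The pooled row assumes a difference common to all sites and ignores the small cost of adjusting for site.

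**The case against.** The case on the other side is substantial.

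- **The aim is exploratory.** No efficacy claim, decision or error rate depends on it, and multiplicity control for such an aim is commonly left to the SAP. This stands, and it is why the point is minor. It does not remove the mismatch, because the protocol itself fixes the site as the unit of testing.
- **An overall comparison is announced.** The opening sentence on reach in G2 does so, and F2 plans to compare interested with uninterested patients without splitting by site. A reader might infer that Aim 3a cannot be answered at all; the documents do not support that, since the same data allow pooling. But the G2 sentence gives no method, and the F2 comparison covers demographic items only and also names no pooled method.
- **Site-level reach is a legitimate question.** Aim 3 is about embedding HOPE in clinics. This also stands, and it is a reason to keep showing site results.
- **The figures rest on assumptions.** A reader might infer that false differences are nearly certain. That needs many sites or the two-comparison reading: with one three-group test at 3 sites the chance is 60%. A reader might also infer that every site test is too small to detect real differences. That is not general: at 5 sites with 3 to 10 comparators per participant, power for 0.5 SD is 85–91%. F2 also plans site numbers in proportion to eligible patients, so larger sites would do better than an equal split suggests, and smaller ones worse.
- **False positives and missed selection are alternatives.** The first calculation assumes no true difference and the second a common one. They should not be presented as happening together.

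**Conclusion.** The point holds as a mismatch between aim and method. The reach tests in G2 are specified only by site, while Aim 3a asks about participants as a whole, so the specified tests do not directly answer it.

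At every site count examined, and on either reading of the tests, pooling gives fewer chance findings and more power for a modest difference common to all sites. For 0.3 SD, per-site power is about 18–75%, against 91% or more pooled. Pooling does not abolish chance findings: 26–51% remains for at least one across the variables, which is a reason to report estimates with intervals and not to rely on p-values.

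The sizes depend on the assumed 3 to 10 equal sites, 0.05 per test and the comparator ratios, none of which the protocol gives. The consequence is confined to an exploratory aim. The primary outcomes, the randomisation and the Aim 1 sample size are unaffected.

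**What to change.** In the reach paragraph of G2:

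1. Make the main analysis one comparison per variable and comparison group, pooled over sites and stratified or adjusted for site. G2 already uses this structure for Aim 1, where the models contain site indicators.
2. Report standardised differences with 95% confidence intervals as the main result.
3. Show site-level figures descriptively, without p-values. If variation between sites is of interest, use one site-by-participation heterogeneity test per variable, which would also help reveal selection running in opposite directions at different sites.

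This is a wording change that uses the same warehouse data. The cost is that site-specific significance statements are given up; for modest differences these are weakly powered at most of the site sizes considered.
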